### Recruitment {15}

Various clinic- and community-based recruitment strategies will be employed to facilitate patient recruitment for the trial. Clinic-based recruitment strategies include referrals from clinicians and healthcare professionals in the study centers, as well as direct phone calls and mailings to patients from OPD records. All clinicians who agree to support the recruitment process will be provided with the detailed inclusion and exclusion criteria. The patients who agree to be contacted will be sent reminder e-mails mentioning the study requirements. Community-based recruitment strategies include web and print advertisements, flyers, and word-of-mouth referral. Advertisements will be run on Facebook and other social media platforms. Identical information regarding the inclusion criteria, estimated duration of assessment and intervention, and study contact details, including anticipated benefits, will be described in all mailings, advertisements, and flyers. All people who approach voluntarily for study participation will be inquired from where they heard about the study.

### Assignment of interventions: allocation

#### Sequence generation {16a}

Random number tables will be used to assign treatments.

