### Trial design {8}

This is a randomized, controlled, double-blinded study determining how CPM changes in response to three types of active exercises in CS-positive CLBP patients. Participants will be randomized to undergo 12 weeks of the motor control exercise (MCE), superficial strengthening (SS), or AE combined with patient education or patient education alone. This active treatment concurrent control design will be used to demonstrate superiority of one exercise group over another. All patients will be allocated in a 1:1:1:1 ratio using random number tables. All participants will receive advice to stay active. Another no-pain control group will also be recruited. The intervention will be provided for 12 weeks. An independent assessor will collect data at baseline (t0), after intervention at 3 months (t1), and at the 6-month follow-up (t2). Outcome measures include CPT for measuring CPM, letter–number sequencing subtest in the Wechsler Adult Intelligence Scale-III Edition (WAIS-III), Stroop neurophysiological test, QoL assessed using the abbreviated WHOQOL-BREF questionnaire, isometric muscle strength of spine and hip muscles, the Oswestry Disability Index (ODI) questionnaire, and the Numerical Pain Rating Scale (NPRS). Table 1 and Fig. 1 present the study design and flowchart, respectively. The research ethics approval was granted by the Integral University, India (IIAHSR/DO/PT/2022/23), and Composite Regional Centre for Skill Development, Rehabilitation, and Empowerment of Persons with Disabilities, India (CRCL/Ph.D. Data Collection/2021–22/1556). The study is designed according to the Consolidated Standards of Reporting Trials (CONSORT) guidelines and reported according to the Standard Protocol Items: Recommendations for Interventional Trials (SPIRIT) checklist. The study will use a 5 (between subjects − type of exercise interventions: MCE vs. AE vs. SS vs. patient education vs. no-pain control) × 3 (within subjects − time: before vs. after vs. 3 months after the intervention) mixed design.

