## Methods: participants, interventions, and outcomes

### Study setting {9}

The study will be conducted between August 2022 and October 2023. In total, 172 participants (both male and female) aged between 18 and 59 years who have CLBP and are positive for CS-related signs and symptoms will be recruited from the Outpatient Physiotherapy Departments of the Integral University and the Composite Regional Centre for Skill Development, Rehabilitation, and Empowerment of Persons with Disabilities. Similarly, we will recruit a no-pain control population (*n* = 43).

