#### Intervention description {11a}

All patients who report for CLBP management will be continuously enrolled in the study. They will undergo a standardized history taking for recording of their demographic details and will be screened for eligibility. The first author will conduct a complete physical assessment and neurological examination, and the presence of “red flags” will be closely monitored. The patients providing voluntary informed consent will be referred to the outpatient departments (OPDs) of the concerned study center where more detailed evaluations will be conducted.

In case of any doubt about a participant’s capacity to engage in the exercise program, they will be directed to a medical professional for an evaluation. The same process will continue until all participants have been recruited (*n* = 172). The recruited participants will then be randomized to receive one of the three exercise interventions along with patient education or patient education alone. A group comprising healthy volunteers will serve as the control group. The interventions will last for 12 weeks. Follow-up will be conducted 3 and 6 months after the intervention.

Three qualified physiotherapists (PTs) in each center will provide the interventions. All of them have a postgraduate degree in musculoskeletal physiotherapy and an average of 11 years of clinical experience. Before initiation of the study, they will attend a training session discussing the detailed treatment procedures. All PTs will be instructed to adhere to the treatment checklist provided and to complete treatment notes after each session. The participants will be instructed to avoid engaging in any other physical program during the study period and to not exercise at home during the intervention period. All the three participant groups will receive the targeted exercise interventions along with the same health education provided to group 4 participants. In order to manage time as effectively as possible, every exercise group will have 5–7 participants. The participants will be advised to continue the exercises after the treatments are over in order to support self-management.

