### Sample size {14}

The sample size was calculated based on the inhibitory effect of the CPT on the PPT, assuming a standard deviation of 100 kPa for the inhibitory effect across all three exercise groups. A sample size of 30 participants per group provides 87% power for an independent *t*-test at a 2-sided alpha of 0.05 to detect a difference in inhibition of 80 kPa [17] when assuming a minimum difference of 0.47 (equivalent to 10% change) as clinically relevant for the CPM effect [55]. Therefore, anticipating a 30% dropout rate, 43 participants will be recruited for each group.

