#### Concealment mechanism {16b}

A sequentially numbered and sealed envelope will contain details of each successive allocation to a random treatment group. An experienced neutral researcher will be provided with sealed envelopes with randomization numbers imprinted; the randomization numbers to which the intervention groups are assigned will be revealed when the envelopes are opened.

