#### Procedure for unblinding if needed {17b}

Complete blinding of investigators and participants will be attempted. The actual allocation will not be disclosed to members outside the research team. Unmasking will be permitted only under special circumstances in which knowledge of the allocated treatment is necessary for further patient care. The primary investigator will take decisions regarding unblinding in consultation with a physician.

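### The trial has two centres, but neither the described allocation nor the stated ANOVA uses centre, so centre balance is left to chance and centre variance stays in the error

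*Protocol article*

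**What the plan says.** All quotations are from the protocol article.

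- **Allocation.** Sequence generation {16a} is one sentence: "Random number tables will be used to assign treatments". Trial design {8} adds the ratio: "All patients will be allocated in a 1:1:1:1 ratio using random number tables". Concealment mechanism {16b} adds the envelopes: "A sequentially numbered and sealed envelope will contain details of each successive allocation to a random treatment group". Implementation {16c} gives randomisation to a researcher with no part in recruitment, treatment or assessment. None of these sections mentions blocks, strata or a separate envelope series for each centre.
- **Size.** Sample size {14}: "Therefore, anticipating a 30% dropout rate, 43 participants will be recruited for each group". Study setting {9} gives the matching total of 172 patients.
- **Centres.** The abstract calls the trial multi-center, and Study setting {9} names two recruiting departments. Intervention description {11a}: "Three qualified physiotherapists (PTs) in each center will provide the interventions".
- **Analysis.** Trial design {8} and Statistical methods {20a,b} both state a mixed design with group at five levels and time at three, followed by Tukey comparisons. Centre is not a factor. Study limitations adds that gender, body mass index and physical activity will not be considered as confounders.

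**The concern.** Two centres with separate therapist teams may differ in patient mix, treatment delivery and test conditions. Pressure pain threshold after a cold pressor test could plausibly vary with all three. A four-arm trial can handle this by balancing arms within centre at randomisation, by fitting centre in the analysis, or by both. The protocol describes neither.

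What is at stake is precision and the credibility of a particular result. If one arm happens to draw many more of its patients from one centre, part of an observed difference between exercise types could be a centre difference, and the stated model cannot separate the two. A lesser matter is that the plan counts on 43 per arm, while the described method does not show how that number is secured.

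**Working it through.** **Inputs from the protocol.** 172 patients, four randomised arms, 43 per arm; 30 completers per group; SD 100 kPa; difference 80 kPa; two-sided alpha 0.05; power 87%; dropout 30%.

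**Assumed, because the protocol does not give them.** The split of patients between centres (86/86, with 115/57 and 129/43 as alternatives) and the centre difference in the outcome on which arms are compared (0.5 SD, range 0.25 to 0.8).

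**1. The plan's own figures.** Effect size = 80/100 = 0.8. With 30 v 30, power is 87.3% by the normal approximation and 86.1% by the noncentral t. Recruitment = 30/(1 − 0.30) = 42.9, so 43, and 4 x 43 = 172. The figures reproduce.

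**2. Arm sizes if the tables are used without restriction.** The sizes are then multinomial (172; ¼, ¼, ¼, ¼).
- P(exactly 43 in each) = 172!/[(43!)⁴ x 4¹⁷²] = 0.00045.
- SD of one arm = √(172 x 0.25 x 0.75) = 5.7.
- By simulation, the smallest arm averages 36.3 and the largest 49.8. They differ by 10 or more in 74% of allocations.

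**3. What unequal arms cost.** Average power for a pair of arms, simulated with each patient dropping out independently at 30% (noncentral t):

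| Allocation | Average pairwise power | At least one arm below 30 completers |
|---|---|---|
| 43 fixed per arm | 85.9% | 88% |
| Unrestricted | 85.2% | 97% |

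The average loss is 0.7 points. The 88% can be checked exactly: P(Binomial(43, 0.7) ≥ 30) = 0.587, and 1 − 0.587⁴ = 0.88.

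**4. Centre mix of the arms.** Gap between the highest and lowest arm in the share of patients from one centre, by simulation:

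| Centre split | Unrestricted: mean gap | Gap of 20 points or more | Arms fixed at 43, not stratified: mean gap |
|---|---|---|---|
| 86/86 | 16 points | 26% | 16 points |
| 115/57 | 15 points | 21% | 15 points |
| 129/43 | 14 points | 15% | 14 points |

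Fixing the arm sizes leaves the gap unchanged. Only stratification by centre removes it.

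**5. What a centre difference costs.** With equal centres and a difference of δ SD, the between-centre part of the variance is 0.5 x 0.5 x δ², as a share of the within-centre variance:
- δ = 0.5: 0.25 x 0.25 = 6.25%, so the standard error is larger by a factor √1.0625 = 1.03.
- δ = 0.25: 0.25 x 0.0625 = 1.6%.
- δ = 0.8: 0.25 x 0.64 = 16%.

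The same quantity can be read as chance imbalance in one comparison. For two given arms of 43, the difference in centre share has SD √(2 x 0.25/43 x 172/171) = 0.108. Multiplied by δ, the error in the contrast has SD 0.054 of an outcome SD (0.027 to 0.087), against the planned effect of 0.8.

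In a group-by-time analysis, a centre difference that is constant over time cancels out of change from baseline. For that contrast, δ must be read as a centre difference in change.

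**The case against.** The strongest objection is that *unrestricted* is inferred from silence. A random number table is a source of randomness and can equally generate permuted blocks or a shuffled list of 43 per arm. Numbered envelopes prepared in advance fit such a list. A journal article may leave block sizes and strata to the full protocol, and block details are often withheld to protect concealment. This stands against any claim that the trial uses simple randomisation, and step 2 is therefore conditional. It does not dispose of the centre point: the article sets out sequence, concealment, implementation and model, states the model's factors in two places, and uses centre in none of them. Step 4 holds even for a fixed list of 43 per arm.

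A reader might also infer stronger things that the document does not support:

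- *That 1:1:1:1 cannot be delivered.* Simple randomisation is 1:1:1:1 in expectation. It just does not secure 43 in each arm.
- *That the arms will be unbalanced by centre.* Imbalance is a chance risk, and the comparison is unbiased in expectation.
- *That the allocation method is why some arm will fall short of 30 completers.* Dropout alone does this in 88% of trials with arms fixed at 43.
- *That power falls to 79%.* That needs both compared arms to have only 25 completers. When one arm is small the others tend to be larger, and 25 v 32 gives 84%.
- *That the last assignments are predictable.* This needs arms to be closed at 43 and recruiters to know the running totals. The protocol states neither, and an independent researcher performs randomisation. The statement that "The actual allocation will not be disclosed to members outside the research team" concerns unblinding and does not show that recruiters see totals.

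**Conclusion.** The point holds as an inefficiency in a stated design, not as a source of bias. With two centres and separate therapist teams, the protocol describes no balancing by centre and specifies a model without centre. Arms would typically differ by 14 to 16 percentage points in centre share between the extremes, depending on the assumed split. The stated model would carry about 6% extra variance if the centres differ by 0.5 SD, and 1.6% to 16% over the assumed range. If the centres do not differ, nothing is lost.

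That 43 per arm is not secured is secondary: it depends on the tables being used without restriction, and its average power cost is under 1 point. The case for acting rests on how little the remedy costs, not on a large harm.

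**What to change.** In Sequence generation {16a}, state that the independent researcher generates the 1:1:1:1 list from the random number tables in permuted blocks of varying size, stratified by centre, with a separate series of numbered sealed envelopes for each centre.

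In Statistical methods {20a,b}, add centre as a fixed between-subjects factor. In the mixed ANOVA this should bring its interaction with time, so that centre differences in change are also removed.

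The cost is one between-subjects degree of freedom and two envelope series. The researcher, tables and envelope procedure stay as they are.

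Trial status gives recruitment from October 2022 to an expected end in January 2023, so randomisation may already be complete. In that case, state the method actually used, report the arm sizes obtained (by centre as well), and keep the centre term in the analysis.

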#### Concealment mechanism {16b}

A sequentially numbered and sealed envelope will contain details of each successive allocation to a random treatment group. An experienced neutral researcher will be provided with sealed envelopes with randomization numbers imprinted; the randomization numbers to which the intervention groups are assigned will be revealed when the envelopes are opened.

#### Implementation {16c}

An experienced researcher not involved in patient recruitment, providing interventions, evaluating the outcomes, or following up with any participant will perform randomization.

### Assignment of interventions: blinding

#### Who will be blinded {17a}

The present study is designed as a randomized controlled trial. The intervention groups will be blinded from one another and outcome assessors. All outcome measures will be determined by an independent researcher blinded to treatment allocation. The assessor will attend training sessions on assessment procedures where the proposed assessment methods will be discussed in detail. The participants will be instructed to not disclose their intervention allocation to the outcome assessor. They will be informed that the effect of different active exercise programs will be evaluated so that they are unaware of any expected treatment group benefit. Another experienced researcher will feed the collected data into the computer. The researcher conducting the statistical analysis will not be present when the measurements are taken. All physiotherapists providing interventions will be blinded to the results of evaluations, measurements, and questionnaires.

#### Procedure for unblinding if needed {17b}

Complete blinding of investigators and participants will be attempted. The actual allocation will not be disclosed to members outside the research team. Unmasking will be permitted only under special circumstances in which knowledge of the allocated treatment is necessary for further patient care. The primary investigator will take decisions regarding unblinding in consultation with a physician.

### Data collection and management

#### Plans for assessment and collection of outcomes {18a}

All participants will be allotted unique study identifiers independent of any external source data. Using paper forms, data will be initially collected during one-on-one sessions with the participants. All data will be collected in a face-to-face interaction and stored in a secured location. The research team will collaboratively manage the data, and a statistical analyst unaware of the grouping situation or intervention measures will analyze the data.

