#### Strategies to improve adherence to interventions {11c}

All participants will be periodically followed up over telephone. Face-to-face adherence reminder will be provided during therapy sessions or outcome measurement. The participants will be reminded about the following:Importance of adhering to study guidelines.Instructions about interventions, dosages, and the procedure to be followed in case of a missed session.Instructions about assessment and the procedure to be followed in case of a missed session.Instructions about adverse events expected, if any.Instructions about management of adverse events.Telephonic follow-up will be conducted on days 3 and 5 if the patient fails to show up for the scheduled assessment and intervention sessions.Importance of continuing exercises after the study period and maintaining a treatment diary.

Reasons for missing the sessions will be recorded, and strategies for incorporating exercises into everyday activities will be emphasized. From the time of recruitment, the participants will be encouraged to ask any questions, and their queries will be satisfactorily answered.

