#### NPRS

The NPRS is a basic instrument that may be administered even to low-literate adults through a verbal face-to-face interview or telephonic interview; the adults can also self-report their responses [44]. The amount of pain felt by a patient will be subjectively estimated by marking their pain level on an 11-point, 0-to-10 NPRS, with 0 and 10 corresponding to no pain intensity and maximum pain intensity, respectively [45].

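### The rule that all data be collected face to face is fixed too tightly: it gives up pain scores that could be taken by telephone from participants who stop attending

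*Protocol article*

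**What the plan says.** Section {18a} of the protocol article fixes both setting and mode. "Using paper forms, data will be initially collected during one-on-one sessions with the participants", and then "All data will be collected in a face-to-face interaction and stored in a secured location". Neither sentence allows for a participant who cannot or will not come in.

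Four other places bear on this:

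- **NPRS section.** The scale may be given even to "low-literate adults through a verbal face-to-face interview or telephonic interview; the adults can also self-report their responses".
- **Strategies to improve adherence {11c}.** "All participants will be periodically followed up over telephone", and "Telephonic follow-up will be conducted on days 3 and 5 if the patient fails to show up for the scheduled assessment and intervention sessions". Collecting an outcome in these calls is not mentioned.
- **Outcomes {12}.** A change in average daily NPRS score from baseline to week 12 is part of the primary efficacy endpoint, although the scale is described among the secondary outcomes.
- **Section {20c}.** The team undertakes to keep missing data to a minimum and to analyse by originally assigned group.

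The sample size {14} allows for heavy loss: "anticipating a 30% dropout rate, 43 participants will be recruited for each group".

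**The concern.** The cold pressor test, pressure algometry, strength tests and Stroop test, as described, need the participant in the room. The NPRS does not, by the article's own account. Applying one rule to all of them means that someone who stops travelling to the clinic loses the pain score along with the tests that depend on attendance, even though staff plan to telephone that person.

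Pain is the outcome most likely to be tied to stopping. People may leave because they hurt, because travel is a burden, or because they are disappointed with education alone. Section {11d} also excludes participants expected to need an analgesic or other physiotherapy during the intervention phase. If such losses differ between arms, pain scores from those who stayed give a distorted contrast, and the analysis by assigned group has gaps that were partly avoidable.

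**Working it through.** **Step 1. The plan's own figures.** Inputs from Sample size {14}: 30 per group, difference 80 kPa, SD 100 kPa, two-sided alpha 0.05, dropout 30%.

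- Standard error = 100 × √(2/30) = 25.8 kPa; 80/25.8 = 3.10; power = Φ(3.10 − 1.96) = 0.873. The exact t-test gives 0.861. The stated 87% reproduces.
- 30/(1 − 0.30) = 42.9, so 43 per group; 4 × 43 = 172 patients. Both match.

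**Step 2. How many pain scores are exposed.** 0.30 × 43 = 12.9 per arm and 0.30 × 172 = 51.6 overall, so about 13 and 52. This is a ceiling: it is the sample-size allowance and includes people who withdraw consent and could not be called.

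**Step 3. What telephone collection could recover.** The share of dropouts who answer is not in the document, so it is varied. With share r, the number per arm with an NPRS is 43 × [1 − 0.30 × (1 − r)].

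| Share answering (assumed) | NPRS per arm | Missing | SE of a group difference, relative to none answering |
|---|---|---|---|
| 0% | 30.1 | 30% | 1.00 |
| 25% | 33.3 | 22.5% | 0.95 |
| 50% | 36.6 | 15% | 0.91 |
| 75% | 39.8 | 7.5% | 0.87 |

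Power for CPM is unchanged, because CPM needs attendance.

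**Step 4. Bias of a completer contrast.** Assumptions, none from the document: dropout of 20% in one arm and 40% in another; dropouts average 1 to 2 NPRS points worse than completers (gap g). With dropout p, the completer mean is too favourable by p × g.

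- Contrast bias = (0.40 − 0.20) × g = 0.20 × g = 0.2 to 0.4 points, favouring the arm that lost more people.

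**Step 5. The same contrast if half the dropouts answer.**

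- *Those who answer are representative of dropouts.* Dropouts then make up (p/2)/(1 − p/2) of the observed scores instead of p. Remaining bias per arm is [p − (p/2)/(1 − p/2)] × g. At p = 0.40: 0.40 − 0.20/0.80 = 0.150. At p = 0.20: 0.20 − 0.10/0.90 = 0.089. Difference = 0.061, so about 0.06 to 0.12 points.
- *Those who answer resemble completers.* The observed mean does not move, and the bias stays at 0.2 to 0.4 points.

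**The case against.** The case for leaving the rule alone has several parts.

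- **One mode for everyone is defensible.** It avoids mixing telephone and in-person scores. This stands as the price of a fallback, but a recorded mode can be examined and an absent score cannot.
- **No contradiction.** A reader might infer that the NPRS section and {18a} contradict each other. They do not: the NPRS section describes what the instrument permits and does not plan telephone collection.
- **The calls may do more than remind.** A reader might infer from {11c} that they serve only as reminders. The article does not say so; nor does it say who makes them. They also follow missed intervention sessions, so an assessor who joined them could learn the allocation that {17a} requires to be hidden. This stands and shapes the fix.
- **Loss is already addressed.** Section {18b} offers flexible scheduling, and {20c} names likelihood-based, selection and pattern-mixture models. Rescheduling does not reach someone who has stopped attending, and the models rest on assumptions that the observed data cannot test. The bias in the working is, however, for a plain completer contrast, not for those models.
- **The benefit is limited.** The trial is sized on CPM, which a call cannot supply. Section {20a,b} sets a per-protocol analysis for the primary outcome, so recovered scores might enter only the analysis by assigned group in {20c}. One call gives a single rating, not the average daily score named in {12}. All of this stands, although a daily average is itself hard to obtain if every score must be taken in person and sessions are twice weekly.

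**Conclusion.** The point holds as a rule drawn too widely. Followed literally, {18a} gives up pain scores that the article's own description of the NPRS makes obtainable, for up to about 13 of 43 participants per arm.

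The likely effect on the contrast is modest. Under the assumed 20% versus 40% dropout and a 1 to 2 point gap, it is 0.2 to 0.4 points, or 10 to 20% of the 2-point NPRS reduction that {20a,b} treats as clinically important. How much a telephone fallback removes depends on who answers: roughly 70% if answerers represent dropouts (1 − 0.061/0.20 = 0.69), nothing if they resemble completers. A reader might infer that halving the missing scores halves the bias; neither case gives that result.

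A reader might also infer that disability and quality of life could be recovered in the same way. The article supports telephone use for the NPRS only. It does not establish it for the 10-item ODI or the 24-item WHOQOL-BREF.

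The change is worth making because it is cheap and serves the commitment in {20c}, not because the trial fails without it.

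**What to change.** Reword {18a} so that face-to-face collection applies to the sensory, strength and cognitive tests. Then add:

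- For anyone who misses t1 or t2, or who stops the intervention without withdrawing consent, the blinded assessor collects the NPRS by telephone within the visit window. State that window if the full protocol does not already define one.
- This call is separate from the adherence contacts in {11c}, and the participant is reminded not to disclose the allocation.
- The mode of collection is recorded, and a sensitivity analysis examines its influence.
- State how a telephone rating relates to the average daily score in {12}.
- ODI and WHOQOL-BREF by interview are an optional extension, where telephone administration is judged valid.

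The cost is a wording change and one short additional assessor call per missed assessment, with a possible difference between telephone and in-person scores. Missing CPM, strength and cognitive data are not recovered.
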